## Abstract

**Background:**

There is little evidence of whether or not those who have attended cardiac rehabilitation (CR) are meeting the physical activity guidelines recommended for secondary prevention of cardiovascular disease. In healthy individuals, there is evidence, that even if individuals are meeting the physical activity guidelines, the harmfulness of too much sedentary behaviour remains (active couch potato (ACP) phenomenon). Currently, there appears to be no evidence of the ACP phenomenon in those attending CR. The aims of the study are to examine the level of physical activity and sedentary behaviour in those with coronary heart disease (CHD) who have attended CR, and to investigate the potential independent associations between these behaviours and cardio-metabolic health, health-related quality of life, exercise capacity, anxiety and depression.

**Methods:**

A prospective cohort study will be conducted in Australia over 12-months. Baseline data from this study will contribute to an international, multi-centre cross-sectional study (Australia, New Zealand, United States of America, South Africa, Spain, and Portugal). Adults currently enrolled in a 6-week phase II cardiac rehabilitation program with stable CHD and receiving optimal medical treatment +/− revascularisation will be recruited. Outcome measures will be taken at baseline (commence CR), 6 weeks (complete CR), 6 and 12-months. Physical activity and sedentary behaviour will be measured using accelerometry and two questionnaires (Active Australia Survey, Past-Day Adults’ Sedentary Time questionnaire). Health outcomes will include body mass index, waist-to-hip ratio, lipid profile, blood glucose level, quality-of-life (MacNew), exercise capacity (6-min walk test), anxiety and depression (Hospital Anxiety and Depression Scale).

**Discussion:**

There has been limited investigation of the physical activity levels and sedentary behaviour of individuals with CHD attending CR. There are no studies assessing the relationship of these behaviours with health outcomes over the short and medium-term. As in healthy individuals, physical activity and sedentary behaviour may have independent effects on cardiovascular risk factors in people with CHD, which may contribute to recurrent cardiovascular events. If this is so, reducing sedentary behaviour may be a feasible first-line, additional and more achievable strategy to improve the health of those with CHD, alongside traditional recommendations to increase the time spent in moderate-to-vigorous intensity physical activity.

**Trial registration:**

Australian New Zealand Clinical Trials Registry (ANZCTR): ACTRN12615000995572

## Background

Heart disease is the leading single cause of death of men and women in Australia, and is prevalent worldwide [1, 2]. It is estimated that 34 % of all heart attacks in Australia are repeat events [3]. Not only are repeat cardiac events more likely to be fatal, they result in a higher burden of disease cost than initial events, with the total economic cost of repeat cardiac events in Australia amounting to $8.4 billion in 2010 [3].

Internationally, it is recommended that all those with coronary heart disease (CHD) be offered cardiac rehabilitation (CR), a secondary prevention program. It is widely recognised that CR decreases mortality, improves risk profiles, decreases hospital admissions, increases medication adherence and improves quality of life [4–7]. CR programs are usually exercise-based, consisting of either regular exercise alone, or a combination of exercise with education and psychological support. Moderate-intensity aerobic exercise, or physical activity, is considered a core component of CR [5, 8]. CR participants are encouraged to increase their moderate-intensity aerobic physical activity slowly and gradually, aiming to accumulate a minimum of 30 min on most, or all, days of the week, throughout life [8]. However, little is known about how much physical activity these individuals undertake outside of the CR program. It is not clear whether CR participants’ are meeting the physical activity guidelines as recommended for secondary prevention, with some indication that only 8.4 min per day of moderate-to-vigorous intensity physical activity (MVPA) is achieved in the first 12 months following diagnosis of CHD [9–11].

In healthy individuals, there is evidence that even if you do enough physical activity to meet the recommendations, by sitting too much (sedentary behaviour), the harmfulness of too much sitting time remains (the ‘active couch potato’ (ACP) phenomenon) [12]. The few prospective studies that have attempted to research this phenomenon have reached the same conclusion: meeting the public health guidelines regarding physical activity (150 min moderate-to-vigorous intensity aerobic physical activity per week) may not necessarily protect against the possible harmful effects from excessive sedentary behaviour [12, 13]. It appears that the more sedentary you are, the more likely you are to die from any cause, with sedentary behaviour recently being considered an independent risk factor for cardiovascular disease and all-cause mortality [14–16]. There is also some evidence that those with cardiovascular disease or diabetes are more likely to die from any cause if they sit for too long, independent of physical activity [17]. Therefore, it is important to take into consideration sedentary behaviour when working towards secondary prevention in those with CHD, intending to prevent further cardiac events.

To our knowledge there are limited studies assessing the effect of physical activity on health outcomes in people with CHD, with no identified studies assessing the effect of sedentary behaviour [18]. The general aim of the current study is two-fold: a) to assess the physical activity levels and sedentary behaviour (ACP phenomenon) outside the clinic in participants attending a hospital-based phase II CR program over 12 months, b) to assess the potential, independent risk of this behaviour on the cardio-metabolic health, health-related quality of life, exercise capacity, anxiety and depression of CR participants.

## Methods

### Design

A prospective cohort study will be conducted in an Australian hospital-based phase II CR program over 12-months. Baseline data from this study will contribute to an international, multi-centre cross-sectional study (Australia, New Zealand, United States of America, South Africa, Spain, and Portugal). At baseline, participants will be assessed within the first 2 weeks after enrolment in the phase II CR program. In Australia, participants will be assessed again within 2 weeks of finishing the 6-week phase II CR program, and at 6 and 12-months following admission into the phase II CR program. The phase II cardiac CR program included in this study is typical of most contemporary CR programs in Australia. The CR program is multidisciplinary, time-limited (twice a week, 6-weeks), conducted in groups, hospital-based, and has educational and supervised exercise components (one hour education plus one hour exercise) [4].

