### Recruitment

CR nursing staff will recruit consecutive participants for this study within CR sessions. CR Staff will identify potential participants on admission to the phase II CR program and will provide them with details of the study. If potential participants are interested in taking part in the study, CR nursing staff will determine whether they are eligible according to the study inclusion and exclusion criteria, and gain participants’ consent. The flow of participants through the trial is illustrated in Fig. 1. The principal investigator (PI) will visit the CR team prior to participant recruitment and explain the study protocol to all team members. The PI will remain in contact with eligible participants and organise 6 and 12-month data collection to maintain participant retention. If participants are lost to follow-up, any data that has been collected will be used in the data analysis.

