#### Sedentary behaviour and physical activity levels

Self-reported sedentary behaviour will be assessed using the PAST [21]. The PAST is a seven-item instrument that uses past-day recall of sedentary time. It asks about time spent sitting or lying (while awake) on the previous day with questions about time spent sitting or lying while at work, travelling, watching television, using the computer (excluding work), reading (excluding work), hobbies, and any other purposes not reported in the previous items. The PAST questionnaire has been found to have acceptable reliability and validity [21].

Self-reported physical activity will be assessed using the AAS [22]. The AAS has been designed to measure participation in leisure time physical activity and to assess the participant’s knowledge of current public health messages about the health benefits of physical activity. It offers a short and reliable set of questions and applies to 1 week preceding the interview, including walking for transport. The AAS has been reported as reliable and of acceptable validity [23, 24].

A triaxial commercial accelerometer (ActiGraph GT3X, Fort Walton Beach, FL) will be used to objectively assess sedentary behaviour and physical activity. Accelerometers allow an objective measurement of quantity and intensity of movement and have been found to be reliable and valid [25]. Participants will be asked to wear the monitor on their right hip during a typical week for 24 h per day for 7 consecutive days. The raw data collected by the accelerometer, counts, will be used to obtain the time spent in different physical activity intensities [26]. We will use the Freedson Combination energy expenditure algorithm to determine the intensity cut-points [27]. Sedentary behaviour will be defined as ≤ 100 counts per minute. This outcome variable will be used to investigate whether participants have reached the World Health Organisation physical activity guidelines, and to calculate sedentary time.

Both the PAST and the AAS questionnaires will be self-administered, and will be completed at the end of the 7-day accelerometer wear time to cover the same time period.

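### Baseline accelerometer week normally includes supervised sessions that the 6- and 12-month weeks lack, so the comparison of outside-clinic MVPA over time is biased towards a decline

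*Protocol article*

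**What the plan says.** The Background gives the first aim as "to assess the physical activity levels and sedentary behaviour (ACP phenomenon) outside the clinic in participants attending a hospital-based phase II CR program", followed over 12 months. It also describes the knowledge gap as how active these people are away from the rehabilitation programme.

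The Design section sets the baseline timing: "At baseline, participants will be assessed within the first 2 weeks after enrolment in the phase II CR program". The Abstract labels the waves differently: "Outcome measures will be taken at baseline (commence CR), 6 weeks (complete CR), 6 and 12-months". Under Recruitment, "CR nursing staff will recruit consecutive participants for this study within CR sessions", so the programme has begun by the time a participant joins the study.

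On the programme itself, the Design section says "The CR program is multidisciplinary, time-limited (twice a week, 6-weeks" and that it "has educational and supervised exercise components (one hour education plus one hour exercise". On the later waves, "participants will be assessed again within 2 weeks of finishing the 6-week phase II CR program, and at 6 and 12-months following admission".

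The device is worn "during a typical week for 24 h per day for 7 consecutive days" (Sedentary behaviour and physical activity levels). The Statistical analysis section derives sedentary measures per day, averages them over valid days, and expresses one as a percentage of the wear-day. MVPA is used to judge attainment of the activity guideline. A one-way repeated measures ANOVA then tests for change in the Australian sample over 12 months. Neither section distinguishes time in supervised sessions from other wear time.

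**The concern.** The aim and the measure do not describe the same quantity. The aim is behaviour away from the clinic; the measure, as defined, is all behaviour in a week that normally includes clinic exercise.

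The mismatch also differs between waves. Session exercise is present by design at baseline and absent at 6 and 12 months. A participant whose own activity never changes would show lower MVPA at the later waves simply because the sessions have ended. The study sets out to describe short- and medium-term change, so this bears on one of its main descriptive results. A reader could take the end of supervised exercise for a loss of habit after rehabilitation, or could miss a real rise in outside activity that the lost sessions offset.

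**Working it through.** The plan gives no figure for the contribution of sessions, so there is none to reproduce. The check compares the content of each wave's wear week and then bounds the size.

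**Step 1. Session content of each wave.**

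| Wave | Timing in the protocol | Programme sessions in a 7-day wear week |
|---|---|---|
| Baseline | within 2 weeks of enrolment, recruited in sessions | normally present, up to 2 |
| 6 weeks | within 2 weeks of finishing | not settled by the Design wording; the Abstract label suggests none |
| 6 and 12 months | counted from admission | none, since the programme lasts 6 weeks |

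**Step 2. Inputs.**
- Sessions per week: 2 (Design)
- Supervised exercise per session: 60 min (Design)
- Guideline: 150 min of MVPA per week (Background)
- Cited MVPA in the first year after diagnosis: 8.4 min/day, or 8.4 × 7 = 58.8 min/week (Background)
- Sessions caught in the wear week, k: 1 or 2 (assumption)
- Share of the exercise hour that registers as MVPA, s: 25% to 100% (assumption; the protocol gives no intensity data)

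**Step 3. Formulas.**
- Added MVPA per week = k × 60 × s; per day, divide by 7.
- For illustration, suppose outside-clinic MVPA is constant at 58.8 min/week. The baseline total is then 58.8 + added, and the apparent fall when sessions stop is added / (58.8 + added).

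**Step 4. Results.**

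| k | s | Added, min/week | Added, min/day | Baseline total, min/week | Apparent fall |
|---|---|---|---|---|---|
| 1 | 25% | 15 | 2.1 | 73.8 | 20% |
| 1 | 50% | 30 | 4.3 | 88.8 | 34% |
| 1 | 75% | 45 | 6.4 | 103.8 | 43% |
| 1 | 100% | 60 | 8.6 | 118.8 | 51% |
| 2 | 25% | 30 | 4.3 | 88.8 | 34% |
| 2 | 50% | 60 | 8.6 | 118.8 | 51% |
| 2 | 75% | 90 | 12.9 | 148.8 | 60% |
| 2 | 100% | 120 | 17.1 | 178.8 | 67% |

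The last two columns assume that the cited 8.4 min/day excludes sessions. The Background does not say whether it does. The min/day column does not depend on that.

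**Step 5. Guideline.** Two full exercise hours are 120/150 = 80% of the weekly threshold. The illustrative participant crosses 150 min only if s is at least (150 − 58.8)/120 = 76% with both sessions caught.

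**Step 6. Sedentary time.** Two education hours are 120/7 = 17.1 min/day of probable sitting. They may replace sitting that would have happened elsewhere, and the exercise hours may replace sitting too, so the sign of the net effect is not determined.

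**The case against.** The strongest reply is that the article is condensed. It mentions valid days and the wear-day without defining them, so accelerometer processing is evidently left to a fuller document, and the handling of session time could be there too. That has some force: the article does not state that sessions are kept in. But the baseline timing is a design choice fixed here, and the article does specify processing at length (cut-points, bouts, breaks, percentage of the wear-day). Followed as written, it yields a total-wear measure, which conflicts with the aim in the same text.

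A second reply is that outside the clinic may only mean free-living behaviour as opposed to clinic testing. The aims in the Abstract and the objectives in the Discussion carry no such limit. On that reading supervised minutes count, and a fall when they end is a real change in total activity. This is possible, but it fits poorly with the Background, which names activity away from the programme as the unknown. The instruction to wear the device in a typical week does not help either: a programme week is not typical of the later waves.

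A third reply is that the regressions come first in the Statistical analysis section and the ANOVA is called additional. This stands in part. A roughly common session offset within a wave shifts the mean and leaves the slopes largely unchanged.

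A reader might also infer that baseline wear can run to day 21 (14 + 7) and so is not a baseline at all. The text does not support that as the natural reading. Participants are to be assessed within two weeks and the questionnaires are completed at the end of the wear week, so wear would ordinarily end by about day 14.

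**Conclusion.** The point holds for aim (a) and for the comparison over time. The baseline week normally includes supervised exercise that the 6- and 12-month weeks cannot contain. As a measure of outside-clinic MVPA, the contrast is therefore biased towards a decline.

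The size is unknown. With one or two sessions caught and 25-100% of the exercise hour registering as MVPA, the addition is about 2-17 min/day. Even the low end is not trivial beside the cited 8.4 min/day, which may or may not itself include sessions.

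Three stronger conclusions might be inferred, and the document does not support them:
- **An observed decline is an artefact.** The net change need not be a decline, since a true rise in outside activity could hide the bias, and a true fall could add to it.
- **Baseline guideline attainment is overstated.** That depends on whether attainment is meant for outside-clinic or total activity. The 150-minute threshold as cited carries no exclusion for supervised exercise.
- **Sedentary time is biased in a known direction.** It is not, for the reason in the working.

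**What to change.** Record the start and end time of each session attended during every wear week. Derive the aim (a) measures with those windows removed, ending any sedentary bout at the window edge and reducing the wear-time denominator by the same minutes. Report total-wear measures, including total guideline attainment, as secondary. State that the 6-week wear period starts after the last session.

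Alternatively, restate aim (a) as total activity and sedentary behaviour, and say that change after the programme includes the end of supervised sessions.

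The first option costs a simple session log (the protocol does not show that attendance times are already held), some extra processing, and a small loss of wear minutes on session days. The second costs only wording, but gives up the outside-clinic question.

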### Participants

Participants will be eligible to take part in the study if they are aged 18+ and are currently enrolled in the hospital-based phase II cardiac rehabilitation program. Participants will be included if they have stable CHD and are receiving optimal medical treatment +/− revascularisation, that is, coronary artery bypass graft surgery, percutaneous transluminal coronary angioplasty or another transcatheter procedure, or have had a myocardial infarction. Participants will be excluded if they have New York Heart Association class II-IV symptoms of heart failure (or documented signs and symptoms of chronic heart failure, with ejection fraction < 45 %), uncontrolled arrhythmias, severe chronic obstructive pulmonary disease, uncontrolled hypertension, symptomatic peripheral artery disease, unstable angina, uncontrolled diabetes, are unable to perform a submaximal walking test (6-min walk test), or are unable to wear an accelerometer due to disability, for example, if they are confined to a wheelchair. Eligible participants must have adequate English language and cognitive skills.

### Recruitment

CR nursing staff will recruit consecutive participants for this study within CR sessions. CR Staff will identify potential participants on admission to the phase II CR program and will provide them with details of the study. If potential participants are interested in taking part in the study, CR nursing staff will determine whether they are eligible according to the study inclusion and exclusion criteria, and gain participants’ consent. The flow of participants through the trial is illustrated in Fig. 1. The principal investigator (PI) will visit the CR team prior to participant recruitment and explain the study protocol to all team members. The PI will remain in contact with eligible participants and organise 6 and 12-month data collection to maintain participant retention. If participants are lost to follow-up, any data that has been collected will be used in the data analysis.

**Fig. 1 Fig1:**
[figure not shown]
Flow of participants through the trial

### Outcome measures

All study measures will be collected at baseline, 6-weeks, 6 and 12 months. All assessments will be conducted at the hospital where the CR program takes place, and will be carried out by a trained health professional. This excludes the blood samples, which will be collected at pathology collection centres. The PI will ensure that all assessors comply with data collection protocols to promote data quality and minimise measurement error.

The main outcome measures are sedentary behaviour and physical activity levels objectively measured using an accelerometer. Subjective measures of sedentary behaviour (Past-Day Adults’ Sedentary Time questionnaire, PAST) and physical activity (Active Australia Survey, AAS) have also been included in this study as they are commonly employed as outcome measures in the clinical setting due to their low cost and ease of use [19]. Haskell also suggests that physical activity data is best interpreted by adopting a combination of objective and subjective measures [20]. Dependent variables include body mass index (BMI), waist-to-hip ratio (WHR), blood lipid and glucose levels, exercise capacity (6-min walk test, 6MWT), quality of life (MacNew Heart Disease Health-related Quality of Life Questionnaire, MacNew) and anxiety and depression (Hospital Anxiety and Depression Scale, HADS).

#### Sedentary behaviour and physical activity levels

Self-reported sedentary behaviour will be assessed using the PAST [21]. The PAST is a seven-item instrument that uses past-day recall of sedentary time. It asks about time spent sitting or lying (while awake) on the previous day with questions about time spent sitting or lying while at work, travelling, watching television, using the computer (excluding work), reading (excluding work), hobbies, and any other purposes not reported in the previous items. The PAST questionnaire has been found to have acceptable reliability and validity [21].

Self-reported physical activity will be assessed using the AAS [22]. The AAS has been designed to measure participation in leisure time physical activity and to assess the participant’s knowledge of current public health messages about the health benefits of physical activity. It offers a short and reliable set of questions and applies to 1 week preceding the interview, including walking for transport. The AAS has been reported as reliable and of acceptable validity [23, 24].

A triaxial commercial accelerometer (ActiGraph GT3X, Fort Walton Beach, FL) will be used to objectively assess sedentary behaviour and physical activity. Accelerometers allow an objective measurement of quantity and intensity of movement and have been found to be reliable and valid [25]. Participants will be asked to wear the monitor on their right hip during a typical week for 24 h per day for 7 consecutive days. The raw data collected by the accelerometer, counts, will be used to obtain the time spent in different physical activity intensities [26]. We will use the Freedson Combination energy expenditure algorithm to determine the intensity cut-points [27]. Sedentary behaviour will be defined as ≤ 100 counts per minute. This outcome variable will be used to investigate whether participants have reached the World Health Organisation physical activity guidelines, and to calculate sedentary time.

Both the PAST and the AAS questionnaires will be self-administered, and will be completed at the end of the 7-day accelerometer wear time to cover the same time period.

